### Implementing the KiVa program

The intervention will be implemented during the 2017 academic year, running from March to November. All schools in Chile have one academic hour per week free of teaching and homework, normally used to promote nonacademic abilities among students. This period of time, already in the curriculum, will be used to deliver the KiVa program.

Universal actions consist of (1) ten 2-h monthly student lessons delivered by a trained teacher and a facilitator (member of the research team), (2) posters encouraging students to support victims and behave constructively when witnessing bullying, (3) a member of the school designated by the school authorities will be present in all school breaks and at lunchtime using a visible KiVa vest to remind everybody that they are in a KiVa school, (4) parents will be informed about bullying through a website, letters and meetings. Finally, in schools receiving the KiVa program with the digital learning environment there will be (5) a tablet-based online game, used by the students during and between their lessons. Playing the game, the students will experience bullying situations in a virtual environment where they will have the opportunity to practice the skills learned in the student lessons to deal constructively with these situations.

The KiVa program also includes “indicated actions.” Bullying incidents will be managed by a designated KiVa team in the school (a teacher, a psychologist or any other professional designated by school authorities). These people will organize discussions with the students involved in bullying and will encourage prosocial peers of the victimized students to support them.

The research teams will provide all the material, training and coaching during the study. Certified KiVa trainers (JG and DV) will deliver the training to all teachers and involved school staff during 2 days in the beginning of the academic year. The Chilean team, backed up by the Finnish team, will be coaching and supporting the intervention schools throughout the academic year. The Chilean team will also undertake observations of how the universal and indicated actions are delivered, in order to assure the fidelity to the program.

The school allocated in the partial KiVa program will receive all actions with the exception of the digital game.

### Control arm

The control group will receive the normal teaching activities and, if the study shows that the intervention is effective, they will receive the intervention in the following year.

### Outcome measures

As demographic information, data on child sex and date of birth, family conditions and socioeconomic features will be collected from children and parents. Permission will be asked to have access to the registry of the academic performance as the grade point average (GPA) of the participating students each trimester.

#### Primary outcomes measure

The primary outcome variables, bullying and victimization, will be measured by the 40-item Revised Olweus Bully/Victim Questionnaire [1], identifying self-reported victims, bullies and bully-victims. The questionnaire has been used worldwide to measure the prevalence of bullying and victimization [22, 23], and the effectiveness of antibullying programs [15, 24, 25]. The questionnaire will be translated into Spanish and its psychometric properties will be evaluated during the formative work phase in a cross-sectional survey among 4th to 8th graders in a sample with similar background and vulnerabilities to the one that will participate in the RCT.

#### Secondary outcome measure

Psychosocial adjustment of students will be assessed with the Strengths and Difficulties Questionnaire (SDQ). This questionnaire assesses 25 attributes into five subscales: (1) Emotional symptoms (five items), (2) Conduct problems (five items), (3) Hyperactivity/inattention (five items), (4) peer relationship problems (five items) and prosocial behavior (five items). The first four subscales generate a total score of difficulties (20 items) and the prosocial behavior scale is considered to reflect the personal strengths of individuals. There are versions for parents and teachers of children aged 4 to 16 years [26] and a self-reported questionnaire for children aged 11 to 16 years [27]. The self-reported version has also been used in younger children (aged 8–13 years) with satisfactory results [28]. It has been widely used [29–36] and has demonstrated good psychometric properties [37]. The authors have the permission to use the Spanish version of SDQ and they have already surveyed around 600 parents and children (aged 9 to 15 years) attending state schools, with similar background and vulnerabilities to the schools expected to participate in the RCT, to carry out a study of the validity and reliability of this questionnaire. The parent and child versions of the SDQ will be utilized.

#### Other outcomes

The Psychological Sense of School Membership (PSSM) scale is a self-reported instrument developed to assess the sense of school belonging. The original PSSM scale comprises 18 items: 13 positively worded statements and 5 negatively worded statements. For each statement, students answer on a 5-point scale (1 = not at all true; 5 = completely true). All of these items are related to students’ perceptions of being “accepted, respected, included and supported by others in the school social environment” (p. 80) [38]. It has been widely used – mainly in English-speaking countries – and it has been associated with several variables related to academic achievement such as increased competence and self-efficacy [39], increased school attendance [40] and higher grades [41]. The authors have conducted a validation study with a sample of 1250 early adolescents in Chile [42]. Both exploratory and confirmatory factor analyses provide evidence of an excellent fit for a one-factor solution after removing the negatively worded items. The new 13-item scale has an internal consistency of 0.92. We also have conducted preliminary analyses finding that high school membership was associated with better academic performance, stronger school bonding, a reduced likelihood of school misbehavior and reduced likelihood of substance use. Analyses showed support for the reliability and validity of the PSSM among Chilean adolescents.

### Sample size

To obtain a significant mean difference between groups, we expect to recruit 39 schools allocated on a 1:1:1 ratio. Each arm should include 1495 eligible students. We used the results in a previous study [15] and the clustersampsi command in Stata Software estimating the number of clusters in two arms (full Kiva versus control; and partial KiVa versus control), using the following command:clustersampsi, samplesize mu1(*X1*) mu2(*X*2) sd1(*Y1*) sd2(*Y27*) m(*Z*) rho(*R*)

Where *X1* = mean in arm 1; *X*2 = mean in arm 2; *Y1* = standard deviation (SD) in arm 1; *Y2* = SD in arm 2; *Z* = number of children per school on average (harmonic mean) (*n* = 115); and *R* = intracluster correlation

The three arms will be balanced with respect to school size. All students attending 4th and 5th grade in 2016 at selected schools will participate in the study.

### Data collection

The preintervention assessment will be carried out at the end of the academic year in November (2016), when participants are attending year 4 and year 5, and the post-intervention assessment 1 year later (November 2017) when students are attending year 5 and year 6, respectively. Independent researchers blind to the allocation will supervise the assessments in classrooms; they will receive a full day of training to ensure a fully standardized data collection. Students will fill self-reported questionnaires with the OBVQ, SDQ and PSSM measures during regular school hours. See Table 1 for the explanatory SPIRIT diagram.

**Table 1 Tab1:**
[figure not shown]
Standard Protocol Items: Recommendations for Interventional Trials (SPIRIT) diagram

^*^If any of the KiVa groups is more effective than the control group, schools in the control group will receive the KiVa program during 2018. ^**^Assessment in control-group schools only

### Data management

After the participants have completed the questionnaires, the data will be entered into a secure platform, without identifying information (each participant will be assigned an ID number). The original copies of the instruments will be filed and stored, under lock and key, in the PI’s office, along with the list linking the participants’ names and ID numbers. Only two research assistants, in charge of data entry, and the statistician will have access to the database.

### Data analyses

The data analyses will follow Consolidated Standards of Reporting Trials (CONSORT) guidelines for RCTs [43]. General school features (size, number of teachers, etc.) will be used to compare participating schools with the ones that were invited but did not participate. Descriptive statistics will be used to compare the three arms at baseline. Primary comparative analysis will be conducted on an intention-to-treat basis. We will use multivariable regression to study differences in mean bullying behavior scores (primary outcome) between groups at the end of the intervention, controlling for baseline outcome variable scores and taking into account clustering within classes and schools. Secondary analysis will be conducted considering adjustment for baseline scores, age and sex. Psychosocial adjustment, psychological sense of school membership and academic outcomes will be analyzed with the same approach.

Sensitivity analysis making different assumptions will be conducted to investigate the potential effects of missing data. Multiple imputation will be performed if necessary.

Apart from evaluating the effects of KiVa, the data will enable various other analyses concerning factors associated with bullying problems and at the individual, classroom and school level in the Chilean context.

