### Inclusion criteria

Our sample frame comprised all schools having primary education (year 1 to year 8), mixed-sex, located in Santiago, with two or three classes per year level and having a vulnerability index (School Vulnerability Index – National System of Equality Allocation (IVE-SINAE)) ≥75%. The IVE-SINAE is built taking into account several students’ and parental variables: health, family income, receiving state benefits. This percentage means the proportion of students in a school who are in most need.

All eligible schools will be invited to participate.

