### Recruitment/allocation of schools

Randomization will be performed once all schools are recruited and after baseline in order to obtain balance with respect to size of the schools and level of self-reported victimization. Schools will be randomly assigned to either group with a 1:1:1 allocation as per a computer-generated randomization. An independent statistician will perform the randomization and allocation concealment will be ensured informing the allocation until all students have been recruited into the trial, which takes place after all baseline measurements have been completed (see Fig. 1).

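### School size and school-level baseline victimization balance the allocation, but size is in neither planned model and victimization enters only the victimization model, as the pupil's own score

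*Protocol article*

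**What the plan says.** Recruitment/allocation of schools places randomization after baseline "in order to obtain balance with respect to size of the schools and level of self-reported victimization". The method (stratified, constrained or minimized) is not named. Schools are the randomized units, so the second factor can only act as a school-level quantity. The Sample size section repeats the first factor: "The three arms will be balanced with respect to school size". The trial is planned with 39 schools, 13 per arm.

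Data analyses sets out a multivariable regression whose target is given as "differences in mean bullying behavior scores (primary outcome) between groups at the end of the intervention". The adjustment attached to that regression reads "controlling for baseline outcome variable scores and taking into account clustering within classes and schools". The next model is described thus: "Secondary analysis will be conducted considering adjustment for baseline scores, age and sex". Psychosocial adjustment, school membership and academic outcomes follow the same approach.

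The Primary outcomes measure section names two primary variables: "The primary outcome variables, bullying and victimization, will be measured by the 40-item Revised Olweus Bully/Victim Questionnaire".

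**The concern.** When allocation is forced to be balanced on a prognostic factor, the arm difference varies less from one allocation to another than under simple randomization. A model without that factor cannot see this. It leaves the factor's variation in the residual and reports a standard error that is too large. Intervals are then too wide, the true type I error falls below its nominal level, and a real effect is easier to miss.

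This is more than silence on a detail. Data analyses gives a covariate list for both models, and the list does not match the balancing factors. With 13 schools per arm, school-level covariates are the ones most likely to matter. At 115 pupils per school, the between-school share of the variance of a school mean is ICC / (ICC + (1 − ICC)/115). That is about 78% at an ICC of 0.03 and about 54% at 0.01. Both ICC values are assumptions, because the article gives none.

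**Working it through.** **1. The plan's own figure.** 13 schools × 115 pupils = 1495 per arm, as stated. The 13 schools cannot be re-derived, because the means, SDs and ICC appear only as symbols. Three arm means leave 39 − 3 = 36 school-level degrees of freedom; two added covariates leave 34.

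**2. Which factor is in which model.**

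| Outcome | School size | Baseline victimization |
|---|---|---|
| Victimization | absent | pupil's own score only |
| Bullying | absent | absent (baseline bullying is in) |
| Psychosocial adjustment, school membership, academic | absent | absent (own baseline is in) |

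The secondary model adds age and sex and changes none of these entries.

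**3. Omitting size alone, with baseline victimization in the model.** Let *v* and *s* be the shares of between-school variance explained by victimization and by size; both are assumed. On school means with unit variance:

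- SE without size = √(2(1 − v)/13)
- SE with size = √(2(1 − v − s)/13)
- ratio = √((1 − v)/(1 − v − s))

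For v = 30%, s = 10% the ratio is √(0.70/0.60) = 1.08. For v = 50%, s = 10% it is √(0.50/0.40) = 1.12.

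A school-level simulation agrees. It used 39 schools, three arms, triplets formed within halves of school size by victimization rank, a two-sided 5% *t* test and 6000 runs per cell. Effects were 1.0 (v = 30%) and 0.85 (v = 50%) school-level SDs.

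| v | s | SE, size out → in | Power %, size out → in | Type I %, size out |
|---|---|---|---|---|
| 30% | 0% | 0.326 → 0.328 | 84.3 → 84.2 | 4.9 |
| 30% | 2% | 0.326 → 0.323 | 84.1 → 84.5 | 4.4 |
| 30% | 5% | 0.327 → 0.316 | 84.5 → 86.9 | 4.7 |
| 30% | 10% | 0.328 → 0.303 | 84.4 → 88.6 | 4.0 |
| 50% | 0% | 0.276 → 0.277 | 84.4 → 84.0 | 5.3 |
| 50% | 2% | 0.276 → 0.271 | 85.6 → 84.9 | 4.4 |
| 50% | 5% | 0.277 → 0.263 | 84.9 → 87.3 | 4.2 |
| 50% | 10% | 0.276 → 0.248 | 85.5 → 91.0 | 3.0 |

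The Monte Carlo error of one power figure is about √(0.85 × 0.15/6000) = 0.5 points, so differences below 1 point are noise. The largest loss is 91.0 − 85.5 = 5.5 points. At s = 5% it is 2.4 points in both blocks. In the last row the model without size reports a mean SE of 0.276 while the estimates actually vary with SD 0.260, so the SE is 0.276/0.260 = 1.06 times too large.

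**4. Pupil score against school level.** With 115 pupils per school, the coefficient of a pupil's baseline score is set almost wholly by the within-school slope. If the between-school slope is steeper, the difference between the slopes times the school mean stays in the residual. A second simulation of the victimization outcome assumed ICC 0.03, allocation drawn from the best-balanced 10% of candidates, size explaining 5%, and 3000 runs per cell.

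| Within / between slope | Planned model: type I, power | Both factors added: type I, power |
|---|---|---|
| 0.4 / 0.7 | 4.1%, 72% | 5.3%, 78% |
| 0.3 / 0.8 | 2.4%, 71% | 5.0%, 82% |
| 0.4 / 0.4 | power 60% | power 61% |

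**5. Bullying outcome.** With an assumed school-level correlation of 0.6 between bullying and victimization, adding both factors raised power from 71% to 74% in one setting and from 70% to 75% in another. The outer bound is a model in which nothing stands in for either factor. In the step 3 simulation that gave type I error of 0.5–2.2% and power of 55–73%, against 84–91% with both in. Baseline bullying is in the planned model and should absorb part of this, so the bound is not an estimate.

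**The case against.** The strongest objection concerns how far the omission reaches. A reader who takes Data analyses literally, where bullying behavior is called the primary outcome, might infer that the primary model leaves out both balancing factors altogether. The article does not support that. The Primary outcomes measure section makes victimization a primary variable as well, and the Specific aims list it first. Adjusting for the baseline value of the outcome then puts pupil-level baseline victimization in that model. The two sections' wording on the primary outcome should be reconciled, but that is a separate matter.

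A reader might also infer that power is plainly wasted. That is not supported either. Eligibility is limited to schools "with two or three classes per year level and having a vulnerability index", which narrows the range of size, and nothing in the article says that size predicts bullying. The ICC, variance shares, slopes and balancing method used above are all assumptions. The conservatism depends on how tightly the unnamed method balances the arms. If the factors explain nothing, adding them gains nothing.

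Finally, the error is conservative: it neither biases the effect estimate nor inflates false positives. All of this stands, and it limits the size of the point. It does not remove the mismatch. Size is used in the allocation and is in no model, victimization is absent for every outcome but one, and a pupil's own score is not the school-level factor that was balanced. The reference distribution for the tests is commonly left to an analysis plan and is not part of this point.

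**Conclusion.** The point holds in limited form. The stated covariate lists do not match the stated balancing factors; this follows from the text and needs no assumption. The consequence is conditional: if the factors are prognostic, standard errors are somewhat too large and the tests conservative.

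Under the assumed inputs, omitting school size alone costs from nothing to about 5 points of power, and about 2.5 points or less unless size explains as much as 10% of between-school variance. For the victimization outcome, in a setting where size explains 5%, the loss from lacking both school-level factors was 6 points (72% to 78%) and 11 points (71% to 82%) when the between-school slope exceeded the within-school slope. It was about 1 point when the slopes were equal. For bullying it was 3 to 5 points under the assumed correlation. None of these figures can be fixed from the article. The trial's validity is not in question; the gain is precision from data that it will already hold.

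**What to change.** In Data analyses, state that the primary model for each outcome includes, as fixed covariates, the variables used to balance the randomization (school size and school-level baseline self-reported victimization) alongside the pupil's own baseline score, with clustering by class and school as planned. Enter each factor in the form used for the allocation. If either is to be left out, give the reason.

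The cost is one sentence and two of the 36 school-level degrees of freedom. No new data are needed, because both values must exist before schools can be randomized. If size proves unrelated to outcome, the price is negligible: in the simulation the standard error moved from 0.326 to 0.328.

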### Trial management

The study will comply with local Research Governance requirements.

## Discussion

The proposed study is the first to test the effectiveness of a school-based antibullying program in Chile in a RCT, and the first study evaluating the KiVa program in its Spanish version. Additionally, testing the added value of the digital learning environment will provide important information on whether the online game should be included in case of wide dissemination of the program in Chile.

A model for disseminating the KiVa program outside Finland already exists, and has been implemented successfully in several European countries. Thus, if the program effects are positive, wide implementation in Chile and other Latin American countries is possible in the near future.

There are, however, some potential risks. An obvious threat for the validity of the findings is that the implementation quality remains low in schools that will be recruited into the RCT. To avoid this threat, we will arrange face-to-face training sessions with the school personnel in order to motivate them to implement the KiVa program as intended, as well as ongoing support and coaching during the implementation process.

Another risk might be difficulty in recruiting enough schools into the RCT. To minimize this risk, we will prepare the recruitment carefully and inform the schools in good time, utilizing the excellent networks of the members of the Chilean team.

### Trial status

This study will start recruiting participants in November 2016.

## Abbreviations

CONSORT: Consolidated Standards of Reporting Trials
IVE-SINAE: School Vulnerability Index – National System of Equality Allocation [Índice de Vulnerabilidad Escolar-Sistema Nacional de Asignacion con Equidad]
KiVa: Kiusaamista Vastaan, “against bullying”
MIAP: Survey of Maltreatment and Abuse of Power among Students
OBVQ: Revised Olweus Bully/Victim Questionnaire
PSSM: Psychological Sense of School Membership scale
RCT: Randomized controlled trial
SD: Standard deviation
SDQ: Strengths and Difficulties Questionnaire
